### Data monitoring

The trial will not have a separate Data Monitoring Committee, as the safety risks associated with this study are very low. Consequently, there are no stopping rules for safety. The trial will be overseen by a TSC, which will perform this function.

### Harms

There is minimal risk associated with the intervention. Any adverse event considered by the occupational therapist to be resulting from participation in the trial will be recorded by the occupational therapist on the WORKWELL Treatment Record Form during treatment sessions. This is completed by the six-week review and a copy returned to the CTU Data Manager. If a participant notifies the therapist of any other adverse events after treatment is completed, then the therapist will e-mail the CTU Data Manager, who will record this additionally on the participant’s WORKWELL Treatment Record form.

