### Choice of comparators

As in our feasibility trial, the control group will receive a written work self-help information pack and usual care. We have chosen a self-help information pack, posted to participants, as the control intervention because patients with RA, UIA or PsA often receive little or no work advice from Rheumatology services [6, 7]. “Usual care” could include some patients receiving brief work advice from therapists but many would not. In our feasibility trial, therapists reported that it was more common for patients to receive an information booklet on work and arthritis, although many may not even receive this, if not referred to occupational therapy. We discussed with therapists what the control intervention should be: brief (i.e. about 45 min) work advice; or work information booklets. The therapists’ consensus was that, once they had received training in Workwell, they would find it more personally conflicting to provide only brief work advice to control participants, as they would now know how to provide work rehabilitation. Accordingly, their decision, supported by our patient research partners, was that they preferred not to have the control participants referred to them and that the control group should receive a self-help information pack (which is also provided to the intervention group). This pack ensures all participants receive the same high-quality written information. Additionally, this approach has been used as a control in other JRVR trials [17, 21]. The therapists in our feasibility trial agreed that the pack contained more information within the booklets than the brief advice that they might provide to employed patients. Accordingly, they considered control participants would not be disadvantaged in receiving this pack instead. Indeed, many would be advantaged, as they would not otherwise receive any work information.

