### Interventions

#### Control and intervention groups: treatment regimens

##### Control group

The control group will receive usual care and a written work self-help information pack.

The pack includes a letter encouraging people to work through a self-help flowchart advising on how to identify work problems and find solutions. Four work advice booklets are included, which reference further work resources [32–35].

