**Contextual Factors: Personal**					
Personal appraisal	Job strain [53]	One item: stress currently experienced at work	✓		✓
	Work motivation/ importance/self-efficacy	3 items: motivation, importance and confidence to continue working (0–10 NRS) (0–10 NRS)			
	Disclosure [50]	Disclosure about condition to employer /line manager	✓		✓
	Job satisfaction	Satisfaction with job: 0–10 NRS	✓		✓
	Future job expectations	Two items: concerns about health affecting ability to work in future; and likelihood of leaving job in the next year due to arthritis	✓		✓
Work-Life Balance	Work-life balance [54].	Four items: perceived work-life balance taken from the Work, Health Life Balance Perceptions Scale	✓		✓

Notes: ^a^ the WLQ-25 and WALS will be collected within the Combined WLQ-25 WALS dual scored measure [41]

Each month, employment status and absenteeism will be collected by the Lancashire Clinical Trials Unit via e-mail or telephone

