### Blinding

Due to the nature of the intervention it will not be possible for therapists to be blinded to group allocation. Therapists are informed not to provide the WORKWELL intervention to any other patients. None of the participating sites normally conduct full work assessments and detailed work provision. To reduce the risk of contamination of the control group (i.e. therapists providing control participants with JRVR), WORKWELL therapists will be informed which participants are in the control group. They will enter the participant’s details onto the Control Participant Log within the Trial Therapy site file. Therapists are requested to check with patients whether they are in the WORKWELL trial and check this Log before providing any brief work advice to patients. Participants cannot be blinded to the intervention they receive. However, we will present the study in the Participant Information Sheet as a trial comparing two methods of providing work advice, without any suggestion that one is preferable. The study explanation includes the conflicting evidence from previous trials and that full JRVR is rare in Rheumatology services. Thus, patients will be informed that, in either arm, they will receive more information about managing work problems than normally available. The trial manager and co-ordinating research team are not blinded to group allocation.

Data co-ordination and data entry staff at the CTU responsible for baseline and follow-up questionnaire management and contacting participants to obtain any missing data at follow-ups, will be blinded to group allocation. The CTU trial manager, data manager and information systems team will be unblinded. The Trial Statistician will initially conduct the analyses blinded to group allocation, ignoring the therapist clustering effects as these cannot be accounted for without knowing group allocation. After the results under blinding have been shared, the Trial Statistician will become unblinded and the analyses will be re-run accounting for therapist effects. Adjusting for therapist effects will only impact the precision of estimates, rather than their magnitude. The health economist will be not be blinded as the costs of WORKWELL will be included in the analysis.

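### Adverse events are recorded only by the treating therapist on a WORKWELL form, so adverse-event counts cannot be compared between arms

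*Protocol article*

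**What the plan says.** The Harms section is the only place in the protocol article that describes how adverse events are captured. It sets four conditions.

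- **What is recorded:** "Any adverse event considered by the occupational therapist to be resulting from participation in the trial".
- **By whom and where:** such an event "will be recorded by the occupational therapist on the WORKWELL Treatment Record Form during treatment sessions".
- **When the form closes:** "This is completed by the six-week review and a copy returned to the CTU Data Manager".
- **Afterwards:** "If a participant notifies the therapist of any other adverse events after treatment is completed", the therapist e-mails the CTU Data Manager, who adds the event to the same WORKWELL form.

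For the other arm, the Control group section states: "The control group will receive usual care and a written work self-help information pack". Under Choice of comparators, the therapists' view was that "they preferred not to have the control participants referred to them". The next paragraphs of that section allow control participants to see occupational therapy for other reasons as part of usual care. Therapists do keep a list of controls (Blinding: "They will enter the participant’s details onto the Control Participant Log within the Trial Therapy site file"), but its stated purpose is to prevent contamination.

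**The concern.** Whether an event is counted should not depend on the allocated arm. Here it depends on attending a WORKWELL session, on an unblinded therapist linking the event to the trial, and on a form used for WORKWELL delivery. A control participant meets none of these conditions through the trial itself. If counts were set side by side, a difference would reflect who was asked, and few or no events in the control column would say nothing about that arm.

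A reference rate would be useful. Both arms are encouraged to act on work problems: controls through the self-help flowchart in the pack, WORKWELL participants through action plans and requests for job accommodations. Symptom flare, distress or friction with an employer could follow in either arm. The judgement of minimal risk also rests partly on the absence of serious events in a small feasibility trial, which the definitive trial could help to check.

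**Working it through.** The article gives no adverse-event figure to reproduce, so the main check is to set the provisions side by side. A little arithmetic then gives the size.

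**1. Is there a control-arm route elsewhere in the article?**

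- Criteria for discontinuing: serious events are those the treating therapist identifies as resulting from WORKWELL. Harm from the pack is judged highly unlikely. No recording route is given for controls.
- Blinding: the Control Participant Log holds participants' details, not events.
- Auditing: remote monitoring checks the quality of adverse-event reporting that already exists. It does not create a new source.
- Composition, roles and responsibilities: the Trial Management Group is told of serious adverse events. No source is named for controls.

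None of these adds a route for controls.

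**2. How many participants does the described route cover?**

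Sample size section: 90 per group with 25% attrition gives 90 / (1 − 0.25) = 120 per arm and 2 × 120 = 240, which matches the stated target. The route covers at most 120 / 240 = 50%. The WORKWELL intervention group section anticipates 86% attendance (25/29 in the feasibility trial). 0.86 × 120 ≈ 103 attenders, and 103 / 240 ≈ 43%. The other 17 or so in the WORKWELL arm would have no session at which an event could be recorded.

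**3. For how long?**

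Data collection methods gives a normal intervention length of three to five months, against 12 months of follow-up. Counting all 120 as under active recording throughout treatment:

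- lower: 120 × 3 = 360 person-months
- upper: 120 × 5 = 600 person-months
- total follow-up: 240 × 12 = 2,880 person-months

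The share is 360 / 2,880 = 12.5% to 600 / 2,880 = 20.8%. This is generous, since it ignores non-attendance.

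**4. What do both arms report anyway?**

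- A&E visits and admissions, with reason for admission: 0, 6 and 12 months (Table 1, economic evaluation).
- Monthly contact: "Each month, employment status and absenteeism will be collected by" the CTU (Table 1 notes).
- SF-12 mental health scale and the EQ-5D-5L anxiety/depression item: 0, 6 and 12 months.
- RADAI-5, RAID and hand/wrist pain: 0 and 12 months.

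These allow indirect comparison of some possible harms by arm. None is designated as adverse-event data.

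**5. What does the feasibility evidence exclude?**

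With zero events in n, the one-sided 95% upper bound is 1 − 0.05^(1/n). For n = 29 allocated it is 9.8%; for n = 25 attenders it is 11.3%. Zero in 120 would give 2.5%, but only in an arm where events are looked for.

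**6. What would identical questioning give?**

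The event rates below are assumptions, since the article gives none. With 120 per arm and two-sided 5%, power = Φ[(|p1 − p2| − 1.96·√(2p̄(1−p̄)/n)) / √((p1(1−p1)+p2(1−p2))/n)], where p̄ is the mean of p1 and p2.

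- 5% v 10%: (0.05 − 1.96 × 0.0340) / 0.0339 = −0.49, power 31%
- 5% v 15%: (0.10 − 1.96 × 0.0387) / 0.0382 = 0.63, power 74%
- 1% v 5%: 44%
- 2% v 10%: 74%

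A fair comparison would be possible but mainly descriptive.

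**The case against.** The strongest reply is that nothing in the plan needs an adverse-event comparison. The Objectives contain no harms comparison, the intervention is described as minimal risk, and the Harms section collects trial-attributed events without promising to set the arms against each other. Identical questioning would have limited power. This stands, and it keeps the point modest.

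Four stronger readings are tempting, and the article does not support them.

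- **That harms as a whole cannot be compared.** Step 4 of the working shows that admissions, absence, job loss, pain, disease activity and mental health are self-reported in both arms on the same schedule. The gap concerns adverse events as such.
- **That active recording stops six weeks after entry.** The review is a telephone progress check within a programme that the article elsewhere describes as lasting several months (two to four, three to five, or four to five further months after the first appointment, depending on the section). The sensible reading is that active recording spans the treatment period.
- **That the steering committee would see events from one arm only.** The article gives the committee the monitoring function but does not say what event data it receives.
- **That control-arm events are certain to go unreported.** Controls may meet a therapist for other reasons, and a full trial protocol, not shown, may add a route for serious events. The article nowhere rules this out.

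The last point does not remove the concern. The article specifies who records, what, where and when, and the route it specifies is one-sided. That is more than a detail left to a longer document.

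**Conclusion.** The point holds as a limited one. As written, adverse events enter the record only through an unblinded treating therapist's attribution on a WORKWELL form during treatment, or later if the participant volunteers them. Ascertainment differs by arm, so adverse-event counts cannot be compared between arms, and an absence of recorded events in controls carries no information.

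The described route reaches at most half of those randomised (about 43% at the anticipated attendance). Active recording covers at most about 12.5% to 20.8% of total follow-up time. These figures assume 120 per arm, 12 months of follow-up for all, treatment lasting three to five months, and no further route in the full protocol.

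A reader might infer that the trial's effectiveness result is compromised. It is not: the primary outcome and its analysis do not depend on adverse-event recording. Since no between-arm adverse-event comparison is planned and several possible harms can be compared indirectly, this is an inexpensive improvement and not a fault in the main design.

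**What to change.** Add one adverse-event item, worded identically for both arms and asked whatever the attributed cause, to the existing 6- and 12-month questionnaires. These already reach all participants and are handled by CTU data staff blinded to allocation. Include the item in the telephone minimum data set, so that those who do not return a questionnaire are asked too. Report the answers descriptively by arm.

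Keep the therapist's Treatment Record as a description of events during WORKWELL delivery, and state that it covers that arm only and will not be used to compare arms.

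The cost is a slightly longer questionnaire at two time points (at most 240 × 2 = 480 responses), a minor amendment through the groups named under Protocol amendments, and more events to process. No new visits are needed. Participants know their allocation, so the item equalises the opportunity to report but does not remove differences in willingness to report.

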### Auditing

The Trial Manager or Chief Investigator will conduct at least one on-site monitoring visit per year over the course of the study to all clinical sites to educate, support and solve problems. A site file checklist will be used at the visit to ensure the site file is up to date. The trial manager or chief investigator research team will complete the checklist and arrange for any missing documents to be added. There will also be remote monitoring, by the CTU and Trial Manager, of quality of source documentation, including consent form completion, adverse event reporting, and deviations from the protocol.

The Chief Investigator will permit study-related monitoring, audits and inspections by the Ethics Committee, lead Research and Development department, the University and any NHS Trust Research Governance Managers requiring this. The study will be monitored in accordance with NHS and University Research Governance procedures. The Chief Investigator will ensure that any regulatory authority is given access to all study-related documents and study related facilities. Principal investigators will be asked to audit their site files at the beginning and end of the study using a checklist provided by the University of Salford co-ordinating research centre and to allow study-related monitoring, audits and inspections as above.

### Composition roles and responsibilities of: the co-ordinating centres, trial management group (TMG) and TSC and data analysis team

Management of the trial is joint between the Centre for Health Sciences Research, University of Salford ([name], [name] and [name]) and Lancashire CTU ([name]). The TMG (consisting of the authors and CTU trial staff) will approve documentation, study protocol procedures, advise on ethics application, monitor trial progress by reviewing the trial progress reports, any problems arising, be advised of any Serious Adverse Events, review findings and plan dissemination. The TMG will meet at three to four monthly intervals and receive reports of trial progress. Teleconferences and ad-hoc meetings will be held during the study if issues arise requiring discussion.

The TSC consists of both independent and non-independent members (approved by Versus Arthritis). The TSC will meet four times, act as the Data Monitoring Committee (DMC) and provide trial oversight and data monitoring. The TSC will meet to approve the protocol, advice on procedures and progress, data monitoring and review findings and monitor trial progress by reviewing the trial progress reports. No interim analyses are planned.

### Protocol amendments

Any subsequent modifications to the protocol which may impact on the conduct of the study, potential benefit to the patient or may affect patient safety, will require a formal protocol amendment, agreed by TMG and TSC members, and approved by the approving NRES Ethics Committee prior to implementation and notification to sites.

### Dissemination and author eligibility

The full trial protocol will be available via the University of Salford Institutional Repository on trial completion. Topics suggested for presentation or publication will be circulated to the TMG. Lead authorship and author eligibility for articles will be agreed by the TMG. Findings will be submitted to rheumatology, rehabilitation and trial methodology conferences and journals, as relevant. A summary of findings will be provided to relevant health professional and arthritis patient organizations, requesting these are included in websites and newsletters. We will provide a summary of the findings to trial participants via a newsletter and the trial website. If successful, we will also provide training materials and information resources for therapists in delivery of WORKWELL and disseminate these as above and will make these available online.

### Studies within a trial (SWAT)

In addition to the main WORKWELL trial, one SWAT is being conducted.

#### Pre-notification letter/email sub-study

This SWAT will use a randomised controlled trial, embedded within WORKWELL, to test a pre-notification communication sent 2 weeks before participants are due to be sent their 6-month follow-up questionnaire against a control of no pre-notification. The communication will take the form of a letter for participants who opt to complete questionnaires postally and an email for those who opt to complete electronically. The text in the pre-notification communication has been theory-informed. The reminder letter (or email) will be personalised to include the (typed) name of the participant because there is some evidence that personalising may improve response rates in surveys. Randomisation will be stratified by WORKWELL trial arm (WORKWELL intervention; control) and planned method of questionnaire completion (hard copy; online).

The primary outcome is a valid response (i.e. usable outcome data) for the WLQ-25 total score obtained by any means, no more than 56 days after the scheduled 6-month follow-up time-point. The secondary outcomes are: valid response for WORKWELL trial primary outcome (yes/no) without reminder; number of reminders sent; time to response [or ceasing follow-up] (days); costs per participant retained. As is usual with a SWAT, no formal power calculation was undertaken, as the sample size will be constrained by the number of participants sent a 6-month questionnaire. Binary data will be analysed using logistic regression and time-to-response by a Cox proportional hazards model. All models will adjust for stratification factors. We will present a crude analysis of the ratio of the estimated between-groups difference in costs, divided by the corresponding difference in proportions providing valid responses for the WLQ-25.

## Discussion

This protocol describes a definitive, pragmatic, multi-centre superiority randomised parallel group trial, which aims to determine the effectiveness and cost-effectiveness of job retention vocational rehabilitation for employed people with inflammatory arthritis. The results of this trial will inform rheumatology teams, NHS managers and service commissioners about how to optimise JRVR for people with inflammatory arthritis, and about the resources needed to achieve this and considerations for informing its uptake and use in clinical practice (implementation). We will develop online resources for health professionals to support delivery of WORKWELL JRVR, if successful. These resources will be available to support education of future health professionals and be modified to be available for use by people with arthritis. The results will be published in a variety of media with different target audiences, when available.

## Data Availability

The de-identified datasets generated and/or analysed during the current study will not be publicly available (as specific consent to place data in a public database was not obtained) but will be available from the corresponding author on reasonable request. The UK WES-RC and UK WES-RC Manual are available in the University of Salford Institutional Repository (see reference list). The Workwell Solutions Manual will be freely available online at www.workwelluk.org and www.mskhub.comon completion of the trial.

## Abbreviations

AtW: Access to Work
BQ: Baseline questionnaire
CEA: Cost effectiveness analysis
CDF: Contact details form
CF: Consent form
CTU: Clinical Trials Unit
EQ-5D-5L: EuroQol 5 Dimension 5 Level
GCP: Good Clinical Practice
ICER: Incremental Cost Effectiveness Ratio
ICH: International Council for Harmonisation of Technical Requirements for Pharmaceuticals for Human Use
JRVR: Job retention vocational rehabilitation
NHS: National Health Service
NICE: National Institute for Health and Care Excellence
NRS: Numeric rating scale
OMERACT: Outcome Measures in Rheumatology
OT: Occupational therapist
PSN: Participant Screening Number
PIN: Participant Identification Number
PI: Principal Investigator
PsA: Psoriatic arthritis
PT: Physiotherapist
QALYs: Quality Adjusted Life Years
RF: Research facilitator
RA: Rheumatoid arthritis
Rad: Research Administrator
RADAI-5: RA Disease Activity Index-5
RA-WIS: RA-Work Instability Scale
RAID: Rheumatoid Arthritis Impact of Disease scale
RCT: Randomised controlled trial
REDCap: Research Electronic Data Capture
SWAT: Studies Within A Trial
SD: Standard deviation
SPIRIT: Standard Protocol Items: Recommendations for Interventional Trials
SF-12v2: Medical Outcome Survey Short-Form 12 version 2
TM: Trial manager
TMG: Trial Management Group
TRF: Trial registration form
TSC: Trial Steering Committee
UCLAN: University of Central Lancashire
UIA: Undifferentiated inflammatory arthritis
UK: United Kingdom
USA: United States of America
WALS: Work Activities Limitations Questionnaire
WES-RC: Work Environment Survey- Rheumatic Conditions
WLQ-25: Work Limitations Questionnaire-25
WPAI: Work Productivity and Activity Index
WTI: Work Transitions Index
